### Economic evaluation

The economic evaluation will be performed for the primary outcome (quality of life) and quality-adjusted life-years (QALYs). For estimating quality adjusted life years (QALYs), the patients’ EQ-5D-5L health states will be converted into utility scores using the Dutch tariff [55]. Subsequently, QALYs will be estimated using linear interpolation between the measurement points.

To account for the highly skewed nature of cost data, the Bias Corrected and Accelerated Bootstrap method (5000 replications) will be used to estimate 95% CIs around the differences in costs. Incremental Cost-Effectiveness Ratios (ICERs) will be calculated by dividing the differences in costs by the differences in the primary outcome quality of life and QALYs. For a graphical illustration of the joint uncertainty surrounding costs and effects, bootstrapped cost-effect pairs will be plotted on cost-effectiveness planes. Cost-Effectiveness Acceptability Curves will also be presented, indicating the intervention’s probability of being cost-effective compared with the control for a range of willingness to pay values. Willingness-to-pay values represent the maximum amounts of money that the decision-makers (i.e. relevant stakeholders) are willing to pay per extra unit of effect.

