### Randomization and allocation

Included patients will complete a first (baseline) questionnaire approximately eight weeks before surgery. Thereafter, randomization will be performed at the patient level. Randomization will be performed in a 1:1 ratio using computer-based randomization lists in Excel, developed by an independent statistician of the Epidemiology and Biostatistics department of Amsterdam UMC. Randomization will be pre-stratified by medical centre (with or without eHealth as usual care), operation procedure (total- or unicompartmental knee arthroplasty) and recovery expectations regarding return to work [25], either positive: “I expect to be fully back at work earlier than the average knee arthroplasty patient” or negative: “I expect to be fully back at work later than the average knee arthroplasty patient”. Only for the randomization lists for medical centres that do not have eHealth as usual care, block randomization will be used. The allocation sequence is predetermined by the statistician and cannot be altered by the researchers. The randomization will follow the order of receiving the patient’s digital baseline questionnaire. Patients will be blinded to the randomization to either the control- or the intervention group.

After allocation, each patient will receive an e-mail containing instructions and a link and log-in details to either the ikHerstel app or to the eHealth from their own hospital or clinic (as explained below in the intervention paragraph). The research team will inform the medical team of the corresponding centre and, if a patient is allocated to the intervention group, the patient’s case-manager. If any patient refuses or wishes to withdraw from the study, either during the inclusion period or during the study period, they will continue to receive care as usual only.

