All relevant costs will be measured using online cost-questionnaires with 3-month recall periods. The cost-questionnaire was developed by our department and tailored to the population and intervention under study. Intervention costs include all costs related to the development, implementation, and execution of the intervention (e.g. ikHerstel, GAS and case-manager) and will be estimated using a micro-costing approach. That is, the cost estimate will be based on actual resources depleted, which will be assessed in detail using prospective data collection, and will be valued in accordance with the Dutch manual for costing studies in health care [49, 50]. Other healthcare costs will consist of costs of primary care (e.g. family physician), secondary care (e.g. hospital stay and visits), and medication (both prescribed and over the counter). The cost of occupational healthcare services will consist of costs of visits to the occupational physician or occupational (physio)therapist. If available, other and occupational health care costs will be valued using Dutch standard costs [50]. If unavailable, prizes of professional health care organizations will be used. Medication use will be valued using prices derived from http://www.medicijnkosten.nl. Informal care will be measured by asking patients to report the number of hours per week they received help from family and friends. Unpaid productivity losses will be measured by asking patients to report the number of hours per week that they were unable to perform unpaid activities (e.g. voluntary work). Unpaid productivity losses and informal care will be valued using a recommended Dutch shadow price [50]. Absenteeism (e.g. total number of sick leave days, measured using a slightly adapted version of the iPCQ [51]) and presenteeism (e.g. lower productivity as compared to normal while at work, measured with the WHO-HPQ [52]) will be valued using sex-specific price weights [50]. Using consumer price indices, all costs will be converted to the same reference year. Because the follow-up period of this study is 12 months, it is not necessary to discount costs and effects.

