### Measurements

Digital questionnaires will be administered with the Survalyzer online tool (survalyzer.com), which can be accessed through a link provided via e-mail, to assess all primary and secondary outcome parameters and additional variables at baseline, and 3, 6, 9, and 12 months after surgery. Measurements will be taken from both patients in the intervention and usual care group, regardless of whether they actually followed the intervention (when in the intervention group). The primary outcome parameter and return to work will also be measured every month during the first 6 months. Six weeks after surgery, we will also assess knee functioning (KOOS), pain (VAS), quality of life (EQ-5D-5L) and patient satisfaction. Table 4 shows an overview of our outcome measures, measurement instruments and measurement moments. All relevant costs will be measured using online cost-questionnaires administered at baseline, 3, 6, 9, and 12 months post-surgery.

**Table 4 Tab4:** Outcome measures, measurement instruments and measurement moments

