*** Secondary Outcomes***										
***Return to Work***		X	X	X	X	X	X	X	X	X
***Physical difficulty experienced at work (WORQ)***	X	X	X	X	X	X	X	X	X	X
***Disease specific functional status (KOOS)***	X		X		X			X	X	X
***Pain Intensity (VAS)***	X		X		X			X	X	X
***Quality of Life (EQ-5D-5L)***	X		X		X			X	X	X
***Energy/Fatique (MFI-20)***	X				X			X	X	X

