*** Process***										
***Patient Satisfaction***			X					X		

T_0_ = baseline, ± 6–8 weeks before surgery; T_1_ = 4 weeks after surgery; T_2_ = 6 weeks after surgery; T_3_ = 2 months after surgery; T_4_ = 3 months after surgery; T_5_ = 4 months after surgery; T_6_ = 5 months after surgery; T_7_ = 6 months after surgery; T_8_ = 9 months after surgery; T_9_ = 12 months after surgery

Patients will have two weeks to complete the questionnaire. After approximately one week, a reminder will be sent by e-mail. If after two weeks the questionnaire is not yet completed, an attempt will be made to contact the patient by phone to encourage them to still complete the questionnaire.

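### Linear QALY interpolation from a baseline 6–8 weeks before surgery carries any 6-week arm difference back across the operation, and the QALY window is not tied to the cost window

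*Protocol article*

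**What the plan says.** Effects. The Economic evaluation section converts EQ-5D-5L states to utilities with the Dutch tariff and then states that "QALYs will be estimated using linear interpolation between the measurement points". The ICER divides the cost difference by the QALY difference. The section does not say on which day the QALY window opens.

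Timing of utilities. The Table 4 footnote defines T0 as "baseline, ± 6–8 weeks before surgery". The Randomization and allocation section agrees broadly: "Included patients will complete a first (baseline) questionnaire approximately eight weeks before surgery". The next EQ-5D-5L comes from this sentence in Measurements: "Six weeks after surgery, we will also assess knee functioning (KOOS), pain (VAS), quality of life (EQ-5D-5L) and patient satisfaction". Table 4 then has it at 3, 6, 9 and 12 months. None is scheduled at surgery.

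Timing of costs. The Costs section says: "All relevant costs will be measured using online cost-questionnaires with 3-month recall periods". Measurements lists "online cost-questionnaires administered at baseline, 3, 6, 9, and 12 months post-surgery". Intervention costs are collected separately and prospectively by micro-costing.

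Horizon. The Costs section adds: "Because the follow-up period of this study is 12 months, it is not necessary to discount costs and effects".

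**The concern.** T0 and week 6 are consecutive measurement points, and the operation lies between them. A straight line assumes that utility starts to change at T0 and passes smoothly through surgery. If the arms are equal at T0 and differ at week 6, the line creates a growing difference over the 6–8 weeks before surgery and a sizeable one on the day itself. Case-manager contact and app access begin only 2–4 weeks before surgery (Components 1 and 3), so 2 to 6 weeks of that difference precede any contact with the programme (6 − 4 = 2; 8 − 2 = 6).

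On the cost side, the four post-surgery questionnaires, each looking back 3 months, cover surgery to 12 months. The baseline questionnaire looks back from T0. Questionnaire costs between T0 and surgery are therefore not captured.

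At stake are the QALY-based ICER, the cost-effectiveness plane and the acceptability curve. The trial's hypothesis is faster recovery, so the difference may well be early and fading. The incremental QALY would then be small, and the treatment of the first segment a material share of it. If the programme is ahead at week 6, the stated rule enlarges its QALY gain.

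**Working it through.** The article gives no utility, QALY or ICER figure, so there is nothing to reproduce. What follows compares three ways to apply its rule.

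**Inputs from the article.** EQ-5D-5L at T0 (b = 6 or 8 weeks before surgery) and at 6 weeks, 3, 6, 9 and 12 months after it, taken as weeks 6, 13, 26, 39 and 52.

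**Assumed inputs.** Arms equal at T0. Utility difference in the main scenario: 0.05 at week 6, 0.03 at week 13, 0 from week 26. Two other scenarios: 0.05 held to week 26 and 0 from week 39, and 0.05 held to week 52.

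**Day-0 value on the interpolated line.** Difference at surgery = d × b/(b + 6), where d is the week-6 difference.
- b = 6: 0.05 × 6/12 = 0.0250 (50% of d)
- b = 8: 0.05 × 8/14 = 0.0286 (57% of d)

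**Area from week 6 on, main scenario (utility-weeks).** (0.05 + 0.03)/2 × 7 + 0.03/2 × 13 = 0.280 + 0.195 = 0.475.

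**First segment under each reading, then the total divided by 52.**
- T0 value placed at surgery: 0.05/2 × 6 = 0.150. Total 0.625/52 = 0.0120.
- Line cut at surgery: b = 6 gives (0.0250 + 0.05)/2 × 6 = 0.225, total 0.700/52 = 0.0135; b = 8 gives (0.0286 + 0.05)/2 × 6 = 0.236, total 0.711/52 = 0.0137.
- Integrated from T0: b = 6 gives 0.05/2 × 12 = 0.300, total 0.775/52 = 0.0149; b = 8 gives 0.05/2 × 14 = 0.350, total 0.825/52 = 0.0159.

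The other scenarios have areas from week 6 on of 0.05 × 20 + 0.05/2 × 13 = 1.325 and 0.05 × 46 = 2.300, with the same first segments.

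| Assumed difference | T0 value at surgery | Line cut at surgery | From T0 |
|---|---|---|---|
| 0.05, 0.03, then 0 from 6 months | 0.0120 | 0.0135–0.0137 (+12% to +14%) | 0.0149–0.0159 (+24% to +32%) |
| 0.05 to 6 months, 0 from 9 months | 0.0284 | 0.0298–0.0300 (+5% to +6%) | 0.0313–0.0322 (+10% to +14%) |
| 0.05 to 12 months | 0.0471 | 0.0486–0.0488 (+3%) | 0.0500–0.0510 (+6% to +8%) |
| No difference at week 6 | – | no change | no change |

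The excess of the third reading over the first is 0.5 × d × b/52, or 0.0029–0.0038 QALY for d = 0.05. It is fixed by the week-6 difference alone, so its share grows as the later effect shrinks.

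**Effect on the ICER, main scenario, same cost difference.** Cut at surgery: 0.625/0.700 = 0.89 and 0.625/0.711 = 0.88, so 11% to 12% lower. From T0: 0.625/0.775 = 0.81 and 0.625/0.825 = 0.76, so 19% to 24% lower.

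**Window length.** Integrated from T0, QALYs span 52 + 6 = 58 to 52 + 8 = 60 weeks, against 52 weeks of questionnaire costs.

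**T0 utility as a covariate.** Assume a utility SD of 0.15–0.25, 110 analysed per arm (half of the 220 in the sample size section) and a correlation of 0.3–0.5 between T0 and later utility. The standard error of the chance T0 difference is SD × √(2/110) = 0.020–0.034. Multiplied by the correlation, one standard error carries 0.006–0.017 QALY into an unadjusted comparison. Adjustment shrinks the standard error of the QALY difference by 1 − √(1 − r²), about 5% (r = 0.3) to 13% (r = 0.5).

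**The case against.** A reader might infer that the plan starts QALYs at T0 and so sets a 58–60 week effect against a 52-week cost. The article does not say this. It names no starting day, and its sentence on discounting gives one 12-month follow-up for costs and effects together, which fits a window opened at surgery better. That stands, and it removes any claim of a stated mismatch. It does not rescue the interpolation rule, which still places half or more of the week-6 difference at day 0 when the line is cut at surgery.

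Nor do all costs start at surgery. Micro-costed intervention costs include the pre-surgery contacts, and since randomization follows the baseline questionnaire and the programme starts 2–4 weeks before surgery, some real pre-surgery effect is possible. Setting the day-0 difference to zero would remove that effect while its cost stays in. This also stands, and it is why interpolation from T0 belongs in a sensitivity analysis.

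The +24% to +32% should not be read as the price of a longer window. About half of it comes from the day-0 value (0.0135–0.0137 against 0.0120); the rest is the area before surgery. The extra weeks common to both arms cancel.

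Finally, a reader might call T0 imbalance a bias. In a randomized trial it is sampling error, which the bootstrap already reflects. The article does not exclude adjustment, and its Statistical analyses section already plans multilevel regression with economic evaluations in mind. A journal article may also leave such detail to an analysis plan.

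**Conclusion.** The point holds as a poorly fixed rule with an unanchored window. Three readings of one sentence give three QALY gains. On either reading that follows the line, a benefit at week 6 is partly moved to or before the operation, in the programme's favour. If the programme were behind at week 6, the rule would work against it.

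The size rests entirely on assumed utilities with equal arms at T0: +12% to +14% or +24% to +32% for an early, short effect, +6% to +8% at most for one sustained to 12 months, and nothing without a week-6 difference. The absolute amounts are a few thousandths of a QALY and matter only because the increment may itself be small. Only the QALY-based economic results are affected; the primary effectiveness analysis is not. Adjustment for T0 utility, which neither the Effect analysis covariate list nor the Economic evaluation section names, is a worthwhile gain in precision and not the repair of an error.

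**What to change.** In the Economic evaluation section, before analysis:

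1. Calculate QALYs over 52 weeks from the day of surgery, matching the questionnaire cost window. In the base case, carry the T0 utility forward to day 0 and interpolate from there. Report interpolation from T0 as a sensitivity analysis, because the programme starts before surgery.
2. Estimate the QALY difference in the planned multilevel regression with T0 utility as a covariate. Bootstrap this adjusted difference jointly with costs for the ICER, the plane and the acceptability curve.

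The cost is a few sentences; all the data are already scheduled. The downsides are that T0 utility is assumed stable until surgery, and that the incremental QALY may come out slightly less favourable to the programme.

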### Harms

All (serious) adverse events (i.e. undesirable experiences occurring to a subject during the study) related to the intervention (e.g. complications during or after resuming daily activities according to the recovery plan), reported spontaneously by the patient or observed by the investigator (i.e. research team) or the orthopaedic surgeon, will be recorded in our study database, reported in our article on (cost-)effectiveness and, if necessary, reported to the Medical Ethical Committee of Amsterdam UMC, location VUmc. If unblinding of the allocation is necessary, we will do so.

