### Blinding

Patients will be blinded as both groups receive a form of eHealth, however with a different dose delivered. It will be impossible, however, to blind the researchers, health care providers and case-managers during the data collection, as they will be in contact with patients allocated to the intervention group. After data collection, the data will be pseudonymized and data will be blinded for the researchers during the analyses.

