A few limitations of this study also need to be addressed. First, it is not possible to blind health care professionals in this study, leaving our study with a risk of contamination and bias on this aspect. Orthopaedic surgeons might hypothetically treat patients differently and provide either more or less attention to return to daily life activities. However, previous research has shown that the actual bias due to this is rather limited, and a meta-epidemiological study of Moustgaard et al. [56] showed no average difference in estimated treatment effects in trials with and without blinding of health care professionals. Moreover, the health care professionals will not be involved in data collection, which will likely attenuate the risk of bias in our results. Second, the heterogeneity of our participating centres could also be seen as a disadvantage, as the provided usual care for the control group might vary between centres. We will account for this bias by stratifying the randomization by participating medical centres with and without eHealth. Moreover, in our analyses we will, by using multi-level modelling, statistically adjust for the clustering within surgeons. Furthermore, as this study will only include (self-) employed patients, it might be argued that unemployed patients cannot benefit from our care program. However, it is important to note that this intervention not only aims at an accelerated return to work but also aims to improve return to daily life activities, making this intervention possibly usable for patients of all ages that receive a knee arthroplasty in a future study. Lastly, this intervention was tailored for Dutch orthopaedic patients (using the Dutch –occupational- healthcare system as context), so generalizability to other countries needs to be done with due caution.

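### Only adverse events related to the intervention are recorded, so the control count is zero by definition and adverse events as recorded cannot be compared between arms

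*Protocol article*

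**What the plan says.** The Harms section states which events enter the database: "All (serious) adverse events (i.e. undesirable experiences occurring to a subject during the study) related to the intervention". Its example of a related event is a complication that follows resumption of activities under the recovery plan: "related to the intervention (e.g. complications during or after resuming daily activities according to the recovery plan"). Events come to light when they are "reported spontaneously by the patient or observed by the investigator (i.e. research team) or the orthopaedic surgeon". Those that qualify "will be recorded in our study database, reported in our article on (cost-)effectiveness" and, where needed, go to the ethics committee.

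The Usual care section gives the control arm its own centre's care and eHealth, and says that this eHealth does not focus on return to daily activities. The recovery plan, the step goals, goal attainment scaling and the case-manager belong to the intervention arm (Intervention, components 1 to 3).

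On blinding, the article says of patients: "Patients will be blinded as both groups receive a form of eHealth". Of staff it says: "It will be impossible, however, to blind the researchers, health care providers and case-managers during the data collection".

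**The concern.** The rule selects events by relatedness to the intervention before they are recorded, and that criterion depends on the arm. A patient who never had the programme cannot have an event related to it.

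This matters because of what the programme does. It aims at faster resumption of activities, gives patients classed as fast recoverers more progressive recommendations, and sets rising step goals from week four. The harms one would look for, such as falls, wound problems, readmission or reoperation, also occur after knee arthroplasty without the programme. For a single patient it is often impossible to say whether the programme contributed. An excess shows itself only when all such events are counted in both arms.

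A relatedness filter can fail in two directions. A true excess disappears if the events are put down to ordinary postoperative complications. A spurious one appears if some ordinary complications in the intervention arm are called related, because the control arm has nothing to set against them. The Conclusion raises the possibility that such care could replace usual care, and that would need comparative harm data.

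**Working it through.** **Step 1: the rule set against the arms.** The article gives no adverse event rate and no harms calculation, so there is no figure of its own to reproduce. The main argument is logical.

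- Condition for recording: the event is related to the intervention (Harms).
- Intervention arm: exposed to the recovery plan, app, goal and case-manager, so the condition can be met.
- Control arm: usual care only (Usual care), so the condition cannot be met except through contamination.
- Other sections: none provides for recording all events in both arms, for fixed safety questions, or for a blinded judgement of relatedness.

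Expected recorded control count = 138 × 0 = 0, whatever the true rate. The 138 per arm is from the Sample size calculation section.

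**Step 2: how much goes unrecorded (rates assumed).** Unrecorded control events = 138 × true rate:

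- 5%: 138 × 0.05 = 6.9, about 7
- 10%: 138 × 0.10 = 13.8, about 14
- 20%: 138 × 0.20 = 27.6, about 28

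**Step 3: the two directions of error (counts assumed, for illustration only).**

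(a) True excess of 14 against 7 events. With all events recorded, the difference is 14/138 − 7/138 = 0.1014 − 0.0507 = 0.0507. The standard error is √(0.1014 × 0.8986/138 + 0.0507 × 0.9493/138) = 0.0318. The 95% CI is 0.0507 ± 1.96 × 0.0318, that is −1.2 to 11.3 percentage points. In the extreme case where all 14 intervention events are regarded as ordinary complications, the planned rule reports 0 against 0.

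(b) No true excess, but 6 intervention-arm events are called related. The rule reports 6 against 0, for which Fisher's exact test gives p = 0.030. With 5 against 0 it gives p = 0.060. The article plans no such test; the figures show only how a one-sided filter can look like a signal.

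**Step 4: what full recording could show.** For true rates of 10% and 5% with 138 per arm and two-sided α = 0.05, power is about 35% by the normal approximation and about 27% with Fisher's exact test. In scenario (a) Fisher's p is 0.17. Full recording makes the comparison valid; it does not make it powerful.

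**Step 5: what is already collected in both arms.** KOOS, pain VAS and EQ-5D-5L are measured at 6 weeks and at 3, 6, 9 and 12 months (Measurements, Table 4). The cost questionnaires at 3, 6, 9 and 12 months cover "secondary care (e.g. hospital stay and visits"). None of these is named as safety data.

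**The case against.** The strongest reply is that the article promises no comparative harm result. Harms are not a listed outcome, and the Harms section undertakes only to record and report related events. That is true, so this is a criticism of a design choice and not a contradiction. It does not rescue the rule. The article fixes what enters the database, and no later analysis plan can recover events that were never recorded.

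Four stronger readings are tempting, and the documents do not support them.

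- **That harms cannot be compared at all.** Knee function, pain and health care use are available by arm and give an indirect comparison. The claim holds for adverse events as recorded.
- **That unblinded staff apply the relatedness filter.** The Harms section says who reports or observes events but not who judges relatedness. Judgement by unblinded staff is an inference from the Blinding section. Nor is capture by spontaneous report alone: observation by the research team or surgeon also counts, and the patients who report are stated to be blinded.
- **That the case-manager gives the intervention arm more opportunity to report events.** Component 3 places that meeting two to four weeks before surgery, and no later visit is stated. Postoperative complications would not surface there.
- **That the Harms section flatly contradicts Strengths and limitations, which says "the health care professionals will not be involved in data collection".** That remark concerns bias in the treatment effects, and the outcomes come from patient-completed questionnaires. What remains is a minor tension over the surgeon's role as an observer of adverse events.

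It is also fair to object that the numerical scenarios rest on assumed rates and that the remedy would have low power. Both points stand. They are reasons to present the comparison descriptively.

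**Conclusion.** The point holds in a limited form. The recording rule makes the control count zero by construction, so the adverse events it yields cannot be compared between arms. This follows from the Harms and Usual care sections alone and needs no assumed rate; the one proviso is the absence of contamination. The size of the loss does depend on assumption: about 7 to 28 unrecorded control events for true rates of 5% to 20%. Lack of staff blinding may add to the problem, but only if those staff judge relatedness, which the article leaves open. The defect should be corrected; it does not affect the primary efficacy analysis.

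**What to change.** Change the Harms section so that all serious adverse events and a short prespecified list (for example unplanned readmission, reoperation, fall and wound problem) are recorded in both arms regardless of relatedness. Collect them with fixed questions in the questionnaires already sent at 6 weeks and 3, 6, 9 and 12 months. Tabulate by arm with risk differences and 95% confidence intervals, labelled as descriptive because power is low. Keep relatedness as a secondary classification, and state who judges it and whether that person knows the allocation. One sentence in Strengths and limitations should acknowledge the surgeon's part in observing adverse events.

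For patients already followed up, use the hospital stays and visits in the cost questionnaires. This gives partial coverage only: the reason for a stay may need checking, and falls or wound problems that led to no care cannot be recovered. Inclusion began in October 2020 and was expected to run until about March 2023, so new questions would reach only part of the sample, and the report should say so.

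The cost is slightly longer questionnaires, more events to log, one extra table, and a protocol amendment with the register and ethics notifications that the Trial design section requires for substantial changes. No clinical management is altered.
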